### Randomization and allocation

The randomization schedule will be prepared by the Evidence-Based Medicine Center of the Academy of Integrative Medicine, Fujian University of Traditional Chinese Medicine. The specific randomization lists will be computer-generated using the SAS 8.12 software PLAY PLAN program (SAS software (Beijing) Co., Ltd, [name]) and concealed from the screeners, assessors, and patients by a designer from the Evidence-Based Medicine Center who is not involved in the study. Cards with group assignments and detailed treatment schedules will be prepared by the Evidence-Based Medicine Center and sealed in opaque envelopes. These sealed envelopes will be marked with the patients’ sequential numbers and kept by the screeners who are responsible for the screening of participants. When a patient has been enrolled, written informed consent has been obtained, and the patient has completed the baseline measurements and is confirmed to be an eligible participant, the envelope corresponding to the sequential number of the patient will be transmitted to the acupuncturist. The acupuncturist will open the envelope and perform the intervention (active or sham acupuncture) according to the treatment schedule written on the card. The information of the allocation list will remain confidential and kept by the acupuncturist not involved in participant recruitment or outcome assessment, and this information will not be shared with the data analyzers or outcome assessors.

### Blinding

The outcome assessors will be blinded to the randomization allocation and will not be involved in performance of the interventions. Participants will be blinded to the group allocation and will not know whether they have been treated with active or sham acupuncture. It will be impossible to blind the acupuncturists because they will perform the interventional protocols. However, the acupuncturists will not take part in the outcome measurements or the statistical analyses, and will be requested not to disclose details about their treatment to the outcome assessors or participants. The statistician will be blinded to the group allocation until completion of the statistical analyses.

### Interventions

The intervention scheme originates from the guidelines of diagnosis, treatment, and rehabilitation for CS [20] and has been practiced for some time in the Second People’s Hospital of Fujian Province and the Affiliated Rehabilitation Hospital, Fujian University of Chinese Medicine. We hypothesized that acupuncture for CS neck pain would have a more positive effect in terms of relieving neck pain and recovering neck physiological function than placebo (sham acupuncture). Therefore, participants in the experimental group will receive the active acupuncture treatment, and participants in the control group will receive the sham acupuncture treatment. All participants will receive 25 mg of diclofenac sodium three times a day if their VAS scores exceed 5.

### Active acupuncture

Active acupuncture treatment will be applied to the participants in the experimental group. Active acupuncture stimulation will be performed at the acupuncture points *Jing-jiaji* (EX-B2.C5), *Jing-jiaji* (EX-B2.C6), *Jing-jiaji* (EX-B2.C7), and *Jianzhongshu* (Sl15) on both sides of the body [22]. Sterile single-use acupuncture needles (40 mm in length and 0.30 mm in diameter; Hwato brand, Suzhou Medical Products Factory Co., Ltd., [name]) will be perpendicularly inserted to a depth of 20 to 30 mm at the selected stimulation point. When the treated participants achieve *de qi* sensation (soreness, numbness, distention, and heaviness), electroacupuncture with its anode connected to *Jing-jiaji* (EX-B2.C5) and cathode connected to *Jing-jiaji* (EX-B2.C7) will be performed to stimulate the relevant acupuncture points for 20 minutes by a single experienced acupuncturist using a continuous-wave, 1-Hz frequency and a comfortable strength.

### Sham acupuncture

Sham acupuncture treatment will be applied to the participants in the control group. The operation of sham acupuncture will be same as that of active acupuncture with the exception of the sites and depth used. Sham acupuncture stimulation will be performed at sites 1.5 cm away from *Jing-jiaji* (EX-B2.C5), *Jing-jiaji* (EX-B2.C6), *Jing-jiaji* (EX-B2.C7), and *Jianzhongshu* (Sl15), and the depth of the inserted needles will be controlled within 15 mm. The operation of electroacupuncture in the control group will be same as that in the experimental group.

### Intervention regimen

Patients will be required undergo ten treatment sessions at a frequency of five sessions a week, and the intervention will be completed in 2 weeks. All electroacupuncture procedures will be performed with a Hwato brand SDZ-II electronic needle therapy instrument made by Suzhou Medical Products Factory Co., Ltd. The two groups will be separated from the treatment, which will be performed by a single acupuncturist.

### Follow-up period

During the 12-week unsupervised follow-up period, no participants will undergo special therapy with the exception of routine cervical care. At post-treatment weeks 4, 8, and 12, the outcome assessor will telephone participants to investigate the recurrence of neck pain.

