### Inclusion criteria

To be eligible, participants must fulfill the following criteria: (1) a confirmed diagnosis of CS neck pain in accordance with the diagnostic criteria published by the Chinese Association of Rehabilitation Medicine (2010) [20] and with reference to the *International Classification of Diseases,* 10th edition (ICD-10) codes (http://www.icd10data.com): M47.812 (other spondylosis without myelopathy or radiculopathy (cervical region)); (2) male or female 18 to 60 years of age; (3) with/without positive signs of musculoskeletal system upon physical examination; (4) pain intensity ranging from 3 to 7 points on a visual analog scale (VAS) upon recruitment; (5) no acupuncture or other relative treatment within the last 7 days; and (6) informed consent document has been signed.

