### Outcome measurement

The following baseline descriptive data will be obtained by questionnaire and physical examination: age, sex, marital status, education level, employment status, family history of CS, VAS score of cervical pain, function of cervical vertebrae, and previous health problems. The radiographic severity of cervical vertebral changes will be assessed on X-ray images. A summary of all measures in the trial is shown in Table 1.

**Table 1 T1:** Study assessments, procedures, and timetable

**Items**	**Before grouping**	**First intervention period (5 days/week)**		**Second intervention period (5 days/week)**		**Follow-up Period**		
Time point (day)	0	1 to 7	7	8 to 14	14	42	70	98
Case diagnosis	X							
Inclusion criteria	X							
Exclusion criteria	X							
Informed consent	X							
Baseline information log	X							
Physical examination	X							
Visual analog scale score	X							
Randomization allocation	X							
Neck physiological function examination		X		X				
Intervention and record		X		X				
Adverse events record		X		X				
McGill pain score			X		X			
Northwick Park Neck Pain Questionnaire score	X		X		X			
Short-Form 36 measure	X		X		X			
Neck pain relapse					X	X	X	X

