### Secondary outcome measures

Quality of life will be assessed using the Short Form-36 (SF-36) Questionnaire [23]. Neck pain will be assessed using the McGill Pain Questionnaire [24]. The recovery period is defined as the number of days from the beginning of treatment to recovery of cervical physiological function and will be recorded by the outcome assessors. Relapse of neck pain will be recorded by telephone investigation during the follow-up period.

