### Statistical analysis

The primary outcomes will undergo intent-to-treat analysis based on the initial treatment assignment and focus on assessment of the main effects of the acupuncture treatment for CS at symptoms of CS and function of the cervical vertebrae. Analyses will be performed using IBM SPSS 20 (version 20.0, IBM Corp., New York, NY, USA). The continuous variables and descriptive values will be expressed using means with standard deviations or medians with ranges. For the variables with a normal distribution, statistical comparisons between the groups will be made by using a *t* test. If the variables have a non-normal distribution or ordinal level, statistical comparison between groups will be made using the Mann–Whitney *U* test. Measures with a discrete distribution will be expressed as percentages and analyzed by the *χ*^2^ or Fisher’s exact test as appropriate. The amount of extra diclofenac sodium used between the experiment and control groups will be analyzed, and a general linear model will be applied to adjust its confounding influence if necessary.

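### Treatment for neck pain after day 14 is neither clearly governed nor scheduled for recording, so a treated, pain-free patient can count as not relapsed

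*Protocol article*

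**What the plan says.** Under Interventions: "All participants will receive 25 mg of diclofenac sodium three times a day if their VAS scores exceed 5". No start, end or reassessment date is attached. Under Inclusion criteria, entry requires "pain intensity ranging from 3 to 7 points on a visual analog scale (VAS) upon recruitment", so some participants can be above the threshold from the outset.

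Under Follow-up period: "During the 12-week unsupervised follow-up period", "no participants will undergo special therapy with the exception of routine cervical care". Neither kind of care is defined and diclofenac is not mentioned. The same section says that at the follow-up time points "the outcome assessor will telephone participants to investigate the recurrence of neck pain". Secondary outcome measures agrees: "Relapse of neck pain will be recorded by telephone investigation during the follow-up period". Data collection and management describes the calls in the same way.

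Table 1, introduced as the summary of all the trial's measures, marks one row at days 42, 70 and 98: neck pain relapse. The row "Visual analog scale score" is marked before grouping only.

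Under Statistical analysis: "The amount of extra diclofenac sodium used between the experiment and control groups will be analyzed", with a general linear model to adjust for it where needed. Neither the period nor the outcome is named.

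**The concern.** Two things are left open together. First, the text does not settle whether the diclofenac rule is still in force during follow-up. Second, whatever participants take or seek in those 12 weeks, no contact is scheduled to record it. Relapse is then judged from the presence of pain at the call, with no knowledge of whether treatment is the reason for its absence.

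The Background says that mid-term to long-term benefit is the less certain part of the evidence, and the Discussion says that the trial will address mid-term efficacy. Relapse is the only outcome scheduled after day 14. Although secondary, it carries all the evidence on that aim. Treatment that was never asked about cannot be restored by analysis, and the Trial status section reports that recruitment is under way.

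**Working it through.** **1. The two rules side by side.**

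| | Interventions | Follow-up period |
|---|---|---|
| Who | all participants | all participants |
| When | no dates given | 12 weeks after treatment |
| Diclofenac | given when VAS exceeds 5 | not mentioned |
| Other care | not mentioned | routine cervical care only, undefined |

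Take a participant whose pain returns to above 5 in the third week after treatment. Whether diclofenac applies depends on two things that the text does not state: whether the first rule outlasts day 14, and whether diclofenac is special therapy, routine care or neither.

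**2. What the schedule collects.** In Table 1 the row for the intervention and its record ends in the second treatment week (days 8 to 14). VAS, the trigger, is at day 0 only. Days 42, 70 and 98 carry the relapse row alone. No scheduled item would show treatment use in follow-up.

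**3. What the analysis can reach.** The diclofenac comparison may be workable for the treatment period if use is logged then. It cannot extend past day 14 without data from past day 14, and the adjustment is conditional in any case.

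**4. Possible size.** The protocol gives no relapse rate and no diclofenac rate, so every input here is an assumption. Let p be true relapse (the same in both arms), u the share of an arm treated during follow-up, and m the share of relapses hidden among those treated, with use unrelated to true relapse:

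observed relapse = p × (1 − m × u)

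With p = 40% (sham v active; difference in points):

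| Use, sham / active | m = 0.25 | m = 0.5 | m = 1 |
|---|---|---|---|
| 30% / 30% | 37 v 37 (0) | 34 v 34 (0) | 28 v 28 (0) |
| 30% / 20% | 37 v 38 (1) | 34 v 36 (2) | 28 v 32 (4) |
| 40% / 20% | 36 v 38 (2) | 32 v 36 (4) | 24 v 32 (8) |

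Example: sham 0.40 × (1 − 0.5 × 0.40) = 0.32; active 0.40 × (1 − 0.5 × 0.20) = 0.36. With p = 20% each difference halves. Equal use lowers both rates and creates no difference. Heavier use in the sham arm makes acupuncture look worse than it is.

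**5. Against the trial's precision.** The plan's 198 per group follows from its formula: 2 × ((1.96 + 0.8416) / 3.33)² × 11.83² = 198.1, where 3.33 = 24.04 − 20.71. With 198 per group:

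- 32% v 36%: standard error = √[(0.32 × 0.68 + 0.36 × 0.64) / 198] = 4.8 points, so the 4-point bias is about 0.8 standard errors. The chance of a nominally significant result is about 13%.
- 24% v 32%: standard error = √[(0.24 × 0.76 + 0.32 × 0.68) / 198] = 4.5 points, so the 8-point bias is about 1.8 standard errors. The chance is about 43%, against a nominal 5%.

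**The case against.** The best defence is that the sections can be read together without conflict. The diclofenac rule stands under Interventions, the Intervention regimen section says that the intervention ends after 2 weeks, and follow-up has its own section. This stands far enough to make the point an ambiguity. A reader might infer a flat contradiction, but that needs both open premises in step 1 to be settled one particular way, and no sentence settles them.

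A second defence is that this is a condensed article, and the full call script may already ask about treatment. That is possible. However, Table 1 is presented as covering all measures, and three sections describe the calls as being about recurrence or relapse. If the script does ask, the part of the fix about data collection is already met.

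Third, the protocol does plan to analyse diclofenac use and adjust for it. That answers part of the concern for the treatment period and none of it for follow-up.

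A reader might also infer that 12-week relapse must be distorted one way or the other: hidden by continued treatment, or inflated by stopping diclofenac at day 14. The documents do not support this. Nothing says that diclofenac stops at day 14. If it did, a return of pain in those who had relied on it could be a genuine difference in durability and not a bias. Masking, for its part, biases the comparison only when use is unequal, and no figure in the protocol shows that it is.

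**Conclusion.** The point holds as an ambiguity together with a gap in data collection. The diclofenac rule has no stated end, follow-up care is not defined in a way that places diclofenac, and treatment after day 14 is not scheduled for recording. Relapse rates may therefore be too low in both arms, and the comparison between arms is biased if use differs. Unequal use is plausible, because the trial's own hypothesis implies that fewer acupuncture patients would stay above the threshold, but it is not documented.

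On the assumed inputs the spurious difference is 0 to 8 points. It is less than one standard error in most cases and approaches two only if every relapse among users is hidden and use is twice as common in the sham arm. The NPQ comparison at the end of treatment, on which the sample size rests, is not touched. The change is worth making because it is cheap and the missing information may not be recoverable later.

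**What to change.** 1. Reconcile the Interventions and Follow-up period sections on whether the diclofenac rule applies after day 14, and say what the follow-up terms include. This review takes no position on which rule should hold.
2. In Statistical analysis, state which period and which outcomes the diclofenac comparison and adjustment cover.
3. In the calls at weeks 4, 8 and 12, also ask about any analgesic or other treatment taken for neck pain since the last contact, whether new or continued. Asking only about newly started treatment would miss participants who carry on from the treatment period.
4. Keep relapse as planned for the main analysis. Compare follow-up treatment use by randomised arm.
5. Add a sensitivity analysis that counts treatment for neck pain beyond permitted routine cervical care as relapse. Fix the list of what counts before the allocation is revealed.

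Relapse should not be split by diclofenac status at day 14: that status arises after randomisation and may itself depend on treatment, so the subgroups would no longer be a randomised comparison.

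The cost is two clarifying sentences, one extra question per call and one extra analysis. Relapse rates will be higher in the sensitivity analysis than in the main one. Participants who have already completed follow-up cannot be asked on schedule, so their number should be reported.

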### Outcome measurement

The following baseline descriptive data will be obtained by questionnaire and physical examination: age, sex, marital status, education level, employment status, family history of CS, VAS score of cervical pain, function of cervical vertebrae, and previous health problems. The radiographic severity of cervical vertebral changes will be assessed on X-ray images. A summary of all measures in the trial is shown in Table 1.

**Table 1 T1:** Study assessments, procedures, and timetable

**Items**	**Before grouping**	**First intervention period (5 days/week)**		**Second intervention period (5 days/week)**		**Follow-up Period**		
Time point (day)	0	1 to 7	7	8 to 14	14	42	70	98
Case diagnosis	X							
Inclusion criteria	X							
Exclusion criteria	X							
Informed consent	X							
Baseline information log	X							
Physical examination	X							
Visual analog scale score	X							
Randomization allocation	X							
Neck physiological function examination		X		X				
Intervention and record		X		X				
Adverse events record		X		X				
McGill pain score			X		X			
Northwick Park Neck Pain Questionnaire score	X		X		X			
Short-Form 36 measure	X		X		X			
Neck pain relapse					X	X	X	X

### Primary outcome measures

The primary outcomes are changes in the symptoms of CS and function of the cervical vertebrae. Symptoms of CS will be measured using the NPQ [22]. Function of the cervical vertebrae, mainly including the activity of the cervical vertebrae upon forward bending, lateral bending, and rotation, will be measured using physical examination and assessed by the outcome assessors.

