**Discussion:**

This paper describes the rationale and design of a randomized double-blind, placebo-controlled trial that aims to determine the efficacy and safety of acupuncture intervention for neck pain caused by cervical spondylosis. The primary outcomes are changes in the NPQ score and neck physiological function. Secondary outcome measures include quality of life, adverse events, and relapse of neck pain. If successful, this project will provide evidence of the efficacy and safety of acupuncture for neck pain caused by cervical spondylosis.

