### Sample size

The sample size calculation was based on a reference of a similar intervention in similar patient groups using the same primary outcome instrument [21]. The primary outcome measure is improvement of scores in neck pain as measured with the Northwick Park Neck Pain Questionnaire (NPQ) at the end of treatments. According to previous research [21], the mean and standard deviation of NPQ scores were (24.04 ± 11.83) in the placebo group and (20.71 ± 11.91) in the acupuncture group. The sample size was calculated based on the formula:

(1)$$n_{1}=n_{2}=2{\left(\frac{z_{\alpha /2}+z_{\beta }}{M_{e}-M_{c}}\right)}^{2}\delta^{2}$$

with a type I error of 5% (α = 0.05) and 80% power (β = 0.2). A total of 198 patients are required in each group to show statistical differences between the groups. We estimated that 15% patients will drop out of the study; thus, 456 patients was established as the sample size.

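### The trial is sized on one primary outcome (NPQ at end of treatment) but names two, so the stated 5% error and 80% power are supported for NPQ only

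*Protocol article*

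**What the plan says.** The Sample size section is in the singular: "The primary outcome measure is improvement of scores in neck pain as measured with the Northwick Park Neck Pain Questionnaire (NPQ"), assessed "at the end of treatments". The calculation that follows uses NPQ means and standard deviations only, "with a type I error of 5% (α = 0.05) and 80% power (β = 0.2"), and arrives at 198 per group.

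Three other places use the plural. The Discussion part of the Abstract says: "The primary outcomes are changes in the NPQ score and neck physiological function". The Primary outcome measures section says: "The primary outcomes are changes in the symptoms of CS and function of the cervical vertebrae". It assigns symptoms to the NPQ and describes function as "mainly including the activity of the cervical vertebrae upon forward bending, lateral bending, and rotation". The Statistical analysis section says: "The primary outcomes will undergo intent-to-treat analysis based on the initial treatment assignment", and then names both symptoms and function as their focus. It compares groups variable by variable: "For the variables with a normal distribution, statistical comparisons between the groups will be made by using a" *t* test, with the Mann–Whitney test for non-normal or ordinal variables.

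Table 1 records the NPQ at days 0, 7 and 14. The Primary outcome measures section gives no time point for either outcome. The article gives no expected difference, standard deviation or power for function.

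**The concern.** The article gives two incompatible answers to the question of what the primary hypothesis is. One section fixes a single outcome at a single time and sizes the trial on it. The other three add a second primary outcome that was never sized and that is described as several movements.

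The primary outcome decides what counts as a positive trial. As the text stands, a significant result on NPQ alone, on function alone, or on both could each be presented as the primary finding, with a sentence of the article to support it. The stated error rate and power were derived for only one of these claims.

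**Working it through.** **Inputs.** From the Sample size section: NPQ mean 24.04 (SD 11.83) on placebo and 20.71 (SD 11.91) on acupuncture, a difference of 3.33; α = 0.05, two-sided because the formula uses z for α/2; power 80%; 198 per group. Assumed, because the article does not give them: a 5% test level for function, 80% power for function, and the correlation between outcomes (0 to 0.9).

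**1. Reproduce the plan's figure.** n per group = 2 × (z_α/2 + z_β)² × SD² / difference².

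- SD 11.83: 2 × (1.960 + 0.842)² × 11.83² / 3.33² = 198.1. With z rounded to 1.96 and 0.84, it is 2 × 7.84 × 139.95 / 11.089 = 197.9.
- Pooled SD 11.87: 199.5, rounded up to 200.
- SD 11.91: 200.8, rounded up to 201.

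The stated 198 therefore follows from NPQ alone at two-sided 5% and 80% power. With the pooled SD, power at 198 per group is 79.7%. Function contributes nothing to this figure.

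**2. NPQ alone decides (the Sample size section).** One test at 5% with about 80% power. Both stated figures hold.

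**3. Either outcome can win, each tested at an assumed 5%.**

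- Two independent tests: 1 − 0.95² = 9.75%.
- Two correlated tests, by simulation: 9.1% at correlation 0.5 and 7.1% at 0.9.
- Only if three movements were tested separately alongside NPQ: 1 − 0.95⁴ = 18.5% if independent, 15.6% at correlation 0.5 and 9.4% at 0.9.
- Power to win on at least one outcome does not fall, because NPQ alone supplies about 80%. With two independent outcomes at 80% each it is 1 − 0.2² = 96%.
- If the error rate were held by testing each of two outcomes at 0.025, NPQ power at 198 per group would be 70.9%, and 242 per group would be needed instead of 200 (pooled SD).

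**4. Both outcomes must win, each tested at 5%.**

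- The error rate stays at or below 5%, because a false claim requires rejection of every null hypothesis, including a true one.
- Joint power, if function also has 80%: 0.8 × 0.8 = 64% at correlation 0, and by simulation 69% at 0.5 and 75% at 0.9.

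| Success rule | Error rate | Power for the claim |
|---|---|---|
| NPQ alone | 5% | about 80% |
| Either of two, 5% each | 7.1% to 9.75% | not below about 80% |
| Both | at or below 5% | 64% to 75% |

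Only the first row delivers both stated figures, and it is the row that the Abstract, the Primary outcome measures section and the Statistical analysis section do not describe.

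**The case against.** The strongest reply is that this is a condensed article. A success rule, a multiplicity procedure and the scoring of neck movement commonly sit in a full protocol or analysis plan that is not shown, so their absence is no fault. That stands, and the point does not rest on it. It rests on the article stating both one and two primary outcomes. A further document could choose between the statements, but it could not make both true.

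Three stronger readings are tempting, and the article does not support them.

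- A reader might infer that each primary outcome is tested at 5%. The only level stated belongs to the NPQ calculation, and none is given for function.
- A reader might infer that error rate and power both fail. Under no single rule do they: with either outcome sufficient, the error rate rises but power does not drop; with both required, power drops but the error rate holds.
- A reader might take 18.5% as the size of the problem. That figure needs four independent primary tests, which no section specifies. Function is named as one outcome, and independence between movements of the same neck is implausible.

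It can also be said that the hypothesis in the Interventions section joins pain relief and functional recovery, which fits a rule requiring both, under which there is no inflation of error. This is fair, but the section does not state it as a success rule, and 198 per group was not derived for joint power. Finally, NPQ and its time point are named in advance, and the statistician is blinded until the analyses are complete. This limits selective choice of the primary result but does not settle the status of function.

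**Conclusion.** The contradiction is real and lies within the article itself. The 5% type I error, 80% power and 198 per group are supported for NPQ at the end of treatment only. They cannot both be relied on for a primary claim that includes function.

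The contradiction and the reproduction of 198 from NPQ alone are firm. The consequences are scenarios: a false-positive risk of about 7% to 9.75% if either of two outcomes could win at an assumed 5% each (about 9% to 18.5% only if three movements were tested separately alongside NPQ), or joint power of about 64% to 75% if both must win and function is assumed to have 80% power. The correlations are assumptions too. This should be corrected, and the Trial status section reports that recruitment is ongoing, so the correction can be made before the analysis.

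**What to change.** Name NPQ at day 14 as the sole primary outcome in the Abstract, the Primary outcome measures section and the Statistical analysis section, to match the Sample size section. Make cervical function the first key secondary outcome, defined as one pre-named measure at one time point, and test it at 5% only if NPQ is significant. Day-7 NPQ becomes secondary.

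This changes wording only. Sample size, visits and measurements stay as planned. The cost is that function can no longer carry a positive trial on its own.

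If function is to remain co-primary, state that both outcomes must be significant, define the single function measure and its time point, and restate the power as joint power, which is below 80% at the planned size under the assumptions above. To restore 80% joint power at correlation 0, each outcome needs √0.8 = 89.4% power. For NPQ with the pooled SD that is about 262 per group before dropout, and it also assumes that function reaches 89.4% at that size.
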